Appendix O. WEEKLY MOOD MONITOR

Please rate your **average** level of anxiety, depression and fatigue. Put a number in the box below to indicate your experience. Pick the number that best corresponds to how you have been feeling over the previous week. You will continue to fill this out in the following weeks. After you submit your responses at the bottom of the page, you will be redirected to a graph. This graph will allow you to follow your progress over the course of the program.

--0--------1--------2--------3--------4--------5--------6--------7--------8--------9--------10--

| None | Mild | Moderate | Severe | Extremely Severe |
| --- | --- | --- | --- | --- |

Anxiety

Depression

Fatigue

APPENDIX P. FOLLOW-UP QUESTIONS

1. What did you find most helpful with Maternal Depression Online?

2. What did you find unhelpful with Maternal Depression Online?

3. What specific aspect of the program did you like the most?

4. What particular aspect of the program did you dislike the most?

5. How did you find the support you received once a week from your etherapist?

6. Were there factors that made it difficult to complete the Maternal Depression Online Program?

7. What information do you feel should be expanded on or added to the Maternal Depression Online program to improve the program?

8. Do you feel the program could be improved with a forum of other mothers that you could correspond with online through the program?

9. Do you think the program was as effective as in-person therapy? If yes, why?

10. Would you recommend this program to a friend struggling with postpartum depression?

11. How did participation in the program impact your ability to parent your infant?

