***Introduction***. Postpartum depression (PPD) and sub-clinical PPD affect approximately 8 to 15% of Canadian women following childbirth (Chalmers et al., 2008). The disorder is debilitating and impacts a woman’s quality of life and her ability to care for and connect with her infant. PPD is also related to short- and long-term consequences for the infant (Tronick & Reck, 2009). Unfortunately, PPD is undertreated for reasons including lack of access to providers and limited mobility. Using the internet to deliver therapy is an innovative way to improve access to psychological treatment. Evidence has suggested that internet cognitive behavior therapy (ICBT) results in significantly larger effect sizes compared to all other online interventions (Barak et al., 2008) and that therapist-assisted ICBT (TAICBT) is comparable to in-person CBT (Spek, 2007).While there is evidence to support the efficacy of TAICBT for the treatment of major depression (Cuijpers et al., 2010), to date, researchers have yet to determine whether this modality is efficacious for the treatment of PPD.

***Purpose and Hypotheses****.* The proposed study will determine whether TAICBT is more efficacious than a waitlist control (WLC) condition in reducing depressive symptom severity, anxiety, general stress, parental stress, and for improving quality of life for women with PPD. It is hypothesized that TAICBT participants will demonstrate significantly greater symptom and clinical improvement from pre- to post-treatment on all outcome measures. It is also expected that symptom improvements will be maintained four weeks following the conclusion of treatment. Given that the TAICBT has not been examined in PPD populations, treatment expectancy, satisfaction, and therapeutic alliance will also be investigated. It is hypothesized that: (a)TAICBT participants will report satisfaction with the treatment,(b) significant associations will be revealed between post-treatment therapeutic alliance ratings and symptom changes scores, and (c) treatment expectancy and satisfaction will be moderately correlated with symptom change scores on all outcome measures. To further understand the participants’ experience with TAICBT, ten open-ended questions will be asked.

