***Method****.* Using a randomized controlled design, 58 women will be randomized to receive either TAICBT treatment or assigned to a 7-10 week WLC. Participants assigned to the WLC will receive a pamphlet that includes information on information on PPD and websites for support services offered in Saskatchewan. The intervention will consist of a seven-module TAICBT program adapted for women afflicted with PPD. Each TAICBT participant will be assigned to a therapist who they can correspond with weekly via email. Potential participants will be screened using the **Edinburgh Postnatal Depression Scale** (EPDS; Cox et al., 1987), modules from the **MINI International Neuropsychiatric Interview** (Sheehan et al., 1998), as well as standard screening questions. If deemed eligible, the following additional outcome measures will be administered: (a)**Depression Anxiety Stress Scale- Short Form** (DASS; Lovibond & Lovibond, 1995) to measure levels of depression, stress, and anxiety; (b)**Parenting Stress Index- Short Form** (PSI-SF; Abidin, 1995) to assess stress in the parent-child system; (c) **World Health Organization Quality of Life – BREF** (WHOQOL-BREF; WHOQOL Group, 1998) to assess quality of life;(d) **Therapist Alliance Questionnaire** (TAQ; Kiropoulos et al., 2008, modified from Luborsky’s 1985 HAQ-II) to determine the degree to which participants perceive the relationship with their therapist as helpful; (e) **Treatment Satisfaction Questionnaire-Modified** (TSQ; Cox et al., 1994) to assess the client’s perceived satisfaction with treatment; and (f) **Credibility/Expectancy Questionnaire**(CEQ; Devilly & Borkovec, 2000) to measure credibility and treatment expectancy of the TAICBT treatment. The TAQ, TSQ, and CEQ will only be completed by those participants receiving TAICBT treatment. All other measures will be completed by both groups of participants at pre-treatment and post-treatment (10 weeks after baseline). Following the 7-10 week wait, participants in the WLC group will be contacted, re-screened, and if still eligible, they will be offered the treatment. At this time, the TAICBT participants will be asked to respond to ten open-ended questions regarding their experiences with the program. To provide a longer-term follow-up of depressive symptoms, TAICBT participants will be contacted by telephone four weeks following treatment completion and administered the EPDS and the depression module of the MINI.

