***Analysis****.* Means, standard deviations, and ranges of all scores for all pre- and post-treatment measures will be computed. Independent samples *t*-tests and chi-square tests will be conducted to assess for group differences in demographic data and baseline measures. Treatment efficacy will be determined using repeated measures mixed-model analysis of variances (ANOVAs). Eta square effect sizes will be computed for all outcome measures. The Jacobson and Truax (1991) method will be used to discern clinical significance, and remission and recovery rates will be reported for both groups. Mixed-model ANOVAs along with tests of simple effects and interaction contrasts will be computed to determine if the TAICBT group maintained the expected treatment gains. The open-ended questions will be analyzed using a grounded theory approach.

***Discussion.*** If found effective, the TAICBT program for PPD could benefit not only Saskatchewan mothers’ mental health and quality of life, but also their infants’ physical and psychological health and the family environment.

5. Researcher Qualifications: Describe any special training or qualifications you and/or the research team have - only in cases where the research involves special or vulnerable populations (e.g. children, incarcerated individuals, etc), distinct cultural groups, or the research is above minimal risk, otherwise this section may be omitted.

N/A

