***TAICBT treatment***: Following completion of the baseline measures, the participants in the TAICBT condition will be provided with a login username and password to access Maternal Depression Online, which will be located at the following address: <http://www.onlinetherapyuser.ca>. As part of clinical practice, with client consent, a letter will be sent to the participant’s family physician informing them that their patient is participating in the Maternal Depression Online program (see Appendix N). This is done for two reasons. The first is to verify the client’s identity, and the second reason is to have a contact number in the unlikely case of an emergency. Upon initial login to the website, participants are provided with an information page and consent form (see Appendix G). The participants will then be offered the seven-module online treatment, with each module taking approximately one week to complete. Each module provides education about the disorder and assigns suggested exercises and homework to be completed in consort with an online therapist. The therapist communicates with their client once a week through emails that are contained within the Online Therapy USER website. Upon login for a new module, participants complete a weekly mood monitor (see Appendix O) and provide examples and answers questions from the previous module (see Introduction pages from http://www.onlinetherapyuser.ca/sitemap).

In order to assess change over time, following treatment completion, participants will be emailed the same website link to fluidsurvey.com to complete the post-treatment outcome measures along with measures related to therapeutic alliance (see Appendices H to M). The measures will take approximately 30-45 minutes to complete and will assess change in symptoms over the course of treatment. In addition to the measures, the participants will be asked to respond to a series of follow-up, open-ended questions regarding their experiences with the program (see Appendix P) as well as questions regarding any additional treatment they sought over the 10-week period (see Appendix O).

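### Follow-up question 9 in Appendix P asks for a reason only after a favourable answer, so the reasons solicited on TAICBT versus in-person therapy are one-sided

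*Protocol*

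**What the plan says.** The protocol summary (Purpose and Hypotheses) gives the aim of the qualitative component: "To further understand the participants’ experience with TAICBT, ten open-ended questions will be asked". The Method paragraph repeats the number: "the TAICBT participants will be asked to respond to ten open-ended questions regarding their experiences with the program". The Analysis paragraph names the method: "The open-ended questions will be analyzed using a grounded theory approach".

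The procedure in Section III, item 3 (TAICBT treatment) gives no number and points to the form itself: "the participants will be asked to respond to a series of follow-up, open-ended questions regarding their experiences with the program (see Appendix P".

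Appendix P prints eleven numbered items. Item 9 is "Do you think the program was as effective as in-person therapy? If yes, why". The last item is "11. How did participation in the program impact your ability to parent your infant".

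**The concern.** An open-ended question that feeds a qualitative analysis should invite an explanation whichever way the respondent leans. Item 9 does so in one direction. A woman who judged the program as good as in-person therapy is asked to explain herself; a woman who judged it worse, or who could not say, is not. Themes built from the answers would then draw on reasons requested from one side.

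The subject is not incidental. The Introduction cites evidence that therapist-assisted internet CBT is comparable to in-person CBT, and the recruitment text in Section III offers the program to providers as an alternative to in-person therapy. The randomised control is a waitlist, so there is no in-person arm. If the write-up quotes women on this comparison, the quoted reasons should not have been gathered from one side only.

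Section IV plans coding by the principal investigator and a second researcher. That guards against a slanted reading of the text collected. It cannot supply reasons that were never requested.

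**Working it through.** No formula applies. The check is a reading of the form item by item, followed by a count.

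**1. Direction of each prompt in Appendix P**

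| Item | Subject | Form | Direction invited |
| --- | --- | --- | --- |
| 1 | most helpful | open | favourable |
| 2 | unhelpful | open | unfavourable |
| 3 | liked most | open | favourable |
| 4 | disliked most | open | unfavourable |
| 5 | weekly therapist support | open | either |
| 6 | obstacles to completion | yes/no | unfavourable |
| 7 | what to expand or add | open | improvement |
| 8 | forum with other mothers | yes/no, no probe | improvement |
| 9 | comparison with in-person therapy | yes/no, probe after yes | reasons for yes only |
| 10 | recommend to a friend | yes/no, no probe | either |
| 11 | effect on parenting | open | either |

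Items 1 and 2 are a balanced pair, as are items 3 and 4. Item 9 is the only item whose follow-up depends on the answer, and the condition is the favourable answer.

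**2. Is the comparison asked anywhere else?** The free-text prompts at the end of the Treatment Satisfaction Questionnaire (Appendix L, General Comments) ask for the best part, the worst part and possible improvements. None mentions in-person therapy, and neither does any other item of Appendix P. Item 9 is the only place where the comparison is asked for.

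**3. Who can make the comparison?** Women in psychotherapy elsewhere at entry are excluded (Section III, item 1), so for many participants the comparison must rest on earlier treatment. The full-screen interview (Appendix D) asks whether a woman was previously in treatment, when, and what kind of therapy it was. The kind is recorded as free text and is not coded as in-person or otherwise.

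**4. Count of items.** Items in open form are 1, 2, 3, 4, 5, 7 and 11, which is 7. Items in yes/no form are 6, 8, 9 and 10, which is 4. The total is 7 + 4 = 11. Counting only the open items gives 7, and adding item 9 because it carries a probe gives 7 + 1 = 8. None of these counts gives the ten stated in the summary.

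**5. Number of women affected.** If the 58 women are split equally (an assumption), 58 / 2 = 29 receive TAICBT. The protocol gives nothing from which to predict how many would answer no. With complete response, the number not asked for a reason could be anywhere from 0 to 29. A narrower figure would be a guess.

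**The case against.** The strongest reply is that the form as a whole is balanced. Items 2, 4, 6 and 7 ask for what was unhelpful, disliked, obstructive or missing, and the Treatment Satisfaction Questionnaire adds the worst part and scope for improvement. This stands. A reader might infer from item 9 that the qualitative data in general are one-sided; the documents do not support that.

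Second, the stated purpose and hypotheses concern TAICBT against waitlist, maintenance of gains, satisfaction, alliance and expectancy. None concerns in-person therapy. This also stands. Because there is no in-person arm, a reader might treat item 9 as the trial's only evidence on comparative effectiveness. It is an opinion item, and the plan makes no such comparison.

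Third, a no is itself recorded, a woman can volunteer her reason under items 2, 4 or 5, and the response format is not shown, so she may be free to write more under item 9. This is why the point is limited to what the form *solicits*. It does not remove the point, because the form still requests an explanation from one side only.

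Fourth, a reader might infer from ten against eleven that a question will be dropped, perhaps the last one, which is the only parenting item on the form. Nothing says so. The procedure text refers to Appendix P without a number, and a miscount in the summary is at least as likely. Parenting stress is in any case measured in both groups by the PSI-SF. The mismatch is clerical.

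**Conclusion.** The point holds in a narrow form. Item 9 requests reasons only from women who answer favourably, and no other prompt asks for the same comparison, so the reasons solicited on TAICBT versus in-person therapy lean one way. The defect is the conditional probe on one item of eleven. It affects only the reading of that item in the qualitative analysis; the efficacy results are untouched. The number of women whose reasons go unasked is unknown. The conclusion assumes that the form is administered as printed. It is a minor improvement, worth making because it costs almost nothing.

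**What to change.** - In Appendix P, item 9, keep the question and replace the conditional probe with *Why or why not?*
- When coding item 9, read each answer alongside the earlier-treatment answers in Appendix D, so that views based on experience of therapy can be told apart from views without it. The type of therapy is free text there, so whether it was in person may not always be clear. No new data collection is needed.
- Optionally, add a neutral probe to the other yes/no items (6, 8 and 10), which can be answered in one word and then yield little to code.
- Reconcile the ten questions stated under Purpose and Hypotheses and under Method with the eleven items printed in Appendix P.

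The cost is a few words on one form, a corrected number in two sentences and slightly more text to code. The change is best made before the form is used. If answers have already been collected, the report should say that only women answering yes to item 9 were asked for a reason.

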APPENDIX Q. MOTHERFIRST AND CONTROL CONDITION PAMPHLET^[[10]](#footnote-10)^

**APPENDIX R. 10-WEEK TREATMENT QUESTIONS**
*During the 10-week period, did you seek any of the following services?*

1. Treatment from a medical doctor (e.g., general practitioner)?  Yes  No

- If yes, approximately how many appointments? _____
- Were the appointments specifically related to Postpartum Depression?  Yes  No

2. Treatment from a psychologist or mental health care worker?  Yes  No

- If yes, how many sessions did you receive? ____
- Were the sessions private or publically covered? Private  Public

3. Treatment from a support group?  Yes  No

- If yes, what was the support group for (Postpartum Depression, Mother Support group)? ______________

4. Begin a psychotropic medication (e.g., antidepressant, antianxiety)?  Yes  No

- If yes, what medication did you take?_____________
- What was the dosage of this medication?__________
- For how long did you take the medication? _________(months)

5. Begin taking naturopathic medicine (e.g., vitamins)?  Yes  No

6. Receive naturopathic or homeopathic procedures (e.g., acupuncture)?
 Yes  No

7. Access other treatments for Postpartum Depression?  Yes  No

- If yes, please explain:____________________________

8. Access the Saskatchewan Maternal Mental Health website? Yes  No

**APPENDIX U: LIST OF ALTERNATIVE RESOURCES**

| Online Services Maternal Depression | Description |
| --- | --- |
| Postpartum Depression Support Group http://www.ppdsupportpage.com/ | A website that includes online support groups, discussion forums, and email support. |
| Postpartum Support International  http://postpartum.net/ | A website that includes information on postpartum depression, helpful resources, and free live phone sessions every week. |

| Online Services for Anxiety and Major Depression | Description |
| --- | --- |
| The Depression Center  http://www.depressioncenter.net/ | Offers tools to overcome depression as well as an online support group |
| [e-couch](http://www.ecouch.anu.edu.au/welcome)  http://www.ecouch.anu.edu.au/welcome | Provides free evidence-based information about emotional problems and teaches users strategies for preventing them |
| [Living Life to the Full](http://www.livinglifetothefull.com/index.php?section=page&page_seq=8) http://www.llttf.com/index.php?section=page&page_seq=8 | A cognitive-behavioral life skills course that aims to provide access to high quality, practical and user-friendly training in life skills |
|  |  |
| [Here toHelp](http://www.heretohelp.bc.ca/) http://www.heretohelp.bc.ca/ | A BC-based website that includes tool kits, fact sheets, and discussion forums for depression and anxiety |
| [The STEPS website](http://glasgowsteps.com/) http://glasgowsteps.com/home.php | A site that tells you all about common stress problems and gives you some ideas on how best to tackle them using CBT strategies |
|  |  |
| [Get Self Help](http://www.getselfhelp.co.uk/cbtstep1.htm) http://www.getselfhelp.co.uk/cbtstep1.htm | A mini 7-step self-help course based on CBT techniques that can be applied to many mental health problems |

| National Websites |  |
| --- | --- |
| [Canadian Mental Health Association](http://www.cmha.ca/bins/index.asp) http://www.cmha.ca/bins/index.asp | Government of Canada website with useful resources on a variety of mental health topics |
| [Centre for Addiction and Mental Health](http://www.camh.net/education/index.html)  http://www.camh.net/education/index.html | Canadian information and resources page for the treatment and management of various mental health conditions |
| [CAMIMH - Faces of mental illness](http://letstalk.bell.ca/en/perspective.php#faces)  http://letstalk.bell.ca/en/perspective.php#facesadian | Alliance of Mental Illness and Mental Health (CAMIMH) nominates five Canadians who are prepared to share their personal struggle with mental illness. |

**APPDENDIX W. PROTOCOL TO ADDRESS A CLIENT WHO IS AT RISK OF SUICIDE**

During the screening process, potential clients are asked a series of suicidality questions. If an individual being screened endorses items that suggest suicidal ideation, the screener must adhere to the following steps:

1) Establish rapport with the client and communicate to her willingness to help. Listen to the client in a concerned and empathetic manner, while also assessing their suicidal potential. The questions to obtain the individual’s suicidal potential are located within the Full Screen Interview under the *Suicidality* section in the M.I.N.I. (see Appendix E, Module B). The screener MUST ask all of these questions to adequately assess the individual’s suicide risk. These questions include information on the frequency, intensity, and duration of these thoughts, the specifics of a potential suicide plan, and the individual’s history around suicidality.

2) If the individual receiving screening does have a suicide plan, the screener will ensure that they have all the information about this plan using the SLAP acronym, which includes information regarding the following factors:

- Specificity of the plan: The more specific the plan, the greater the risk of suicide.
- Lethality of the method: The greater the lethality, the higher the risk of suicide.
- Inquire about the general method and how method will be employed.
- Availability of the method.
- Proximity of social or helping resources: The further the client is from support the greater the risk.

Once the screener has assessed the potential client’s suicide risk, they will decide on an appropriate course of action based on the client’s risk of suicide. They should seek supervision as soon as possible for this situation. They must also document the screening, as well as the actions they took.

If the client is at ***high risk*** for suicide (e.g., specific plan, lethal and available method, resources are limited), then the screener should encourage this person to seek immediate medical attention from their physician. If their physician is unavailable, then they should be directed to the emergency room of the nearest hospital. This potential client should be asked to contact someone they feel comfortable speaking with to assist them in going to the doctor or to the hospital.

If the plan appears immediate, the screener is to call 911. The screener should also let the potential client know that they will need to contact their physician to ensure that he or she is aware of their client’s situation, and so that they can monitor the client’s status.

In regards to ***medium suicide risk***, the screener will encourage the client to seek assistance from their local mental health clinic. The screener must also provide the potential client with the mental health clinic’s contact information (i.e., phone number, address). They may also consider contacting the family physician to make him or her aware of the client’s difficulties. If the screener is going to contact the physician, they must let this potential client know.

In the case of ***low risk*** suicidality, the screener should seek a supervisor out in order to determine if the risk of suicide is sufficiently low for the client to participate in online therapy, or if the client should be encouraged to seek in person services. Actions will be taken based on this decision.

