**In the past month did you:**

B1 Suffer any accident? This includes taking too much of your medication accidentally. NO YES 0

IF NO TO B1, SKIP TO B2; IF YES, ASK B1a:

**B**1a Plan or intend to hurt yourself in any accident either actively or passively (e.g. by not avoiding a risk)? NO YES 0

IF NO TO B1a, SKIP TO B2: IF YES, ASK B1b:

B1b Intend to die as a result of any accident? NO YES 0

B2 Feel hopeless? NO YES 1

B3 Think that you would be better off dead or wish you were dead? NO YES 1

B4 Think about hurting or injuring yourself or have mental images of harming yourself, NO YES 4 with at least some intent or awareness that you might die as a result?

How many times? _____

B5 Think about suicide (killing yourself)? NO YES 6

How many times? _____

IF NO TO B5, SKIP TO B7. OTHERWISE ASK:

Frequency Intensity

Occasionally πMild π

Often πModerate π

Very often πSevere π

B6 Feel unable to control these impulses? NO YES 8

| B7 | Have a suicide method or plan in mind (e.g. how, when or where)? | NO | YES | 8 |
| --- | --- | --- | --- | --- |

IF NO TO B7, SKIP TO B9.

NOTE: IF PARTICIPANT HAS A SUICIDE PLAN OR RESPONDS ‘YES’ TO ANY OF THE ITEMS FROM B7 ONWARD, END INTERVIEW AND REFER TO ALTERNATIVE RESOURCES.

B8 Intend to follow through on a suicide plan? NO YES 8

B9 Intend to die as a result of a suicidal act? NO YES 8

B10 Take any active steps to prepare to injure yourself or to prepare for a suicide attempt

in which you expected or intended to die? NO YES 9

How many times? _____

B11 Injure yourself on purpose without intending to kill yourself? NO YES 4

B12 Attempt suicide (to kill yourself)? NO YES 9

A suicide attempt means you did something where you could possibly be injured,

with at least a slight intent to die.

IF NO, SKIP TO B13:

How many times? _____

Hope to be rescued / survive π

Expected / intended to dieπ

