**In your lifetime:**

B13 Did you ever make a suicide attempt (try to kill yourself)? NO YES 4

“A suicide attempt is any self-injurious behavior, with at least some intent (> 0) to die as a result or if intent can be inferred, e.g. if it is clearly not an accident or the individual thinks the act could be lethal, even though denying intent.”

(C-CASA definition). Posner K et al. Am J Psychiatry 164:7, July 2007.

| is at least **1** of the above (EXCEPT B1) coded **yes**?  If yes, add the total points for the answers (B1-B13)  checked ‘yes’ and specify the suicidality score as indicated in the diagnostic box:  make any additional comments about your assessment of this patient’s current  and near future suicidality in the space below:  If you do start having thoughts of suicide, or you begin to have a plan around suicide during this program, please make sure to let your therapist know. Since your therapist may not check their emails every day, it would be best if you phone them. You can also phone the Online Therapy Unit and speak to the co-ordinator for this project, [name]. If you are unable to reach your therapist or the co-ordinator, there is a suicide prevention tab on the website that lists other agencies you can call as well. If you feel as though you are at risk for committing suicide, you can also call 911 for help. | ***NO YES***  ***SUICIDALITY***  ***CURRENT***  1-8 points Low π  9-16 points Moderate π  > 17 points High π   |
| --- | --- |

**Participant must have LOW Current Suicide Risk to participate in program. If > Low, DISCUSS OTHER OPTIONS FOR TREATMENT; DOCUMENT DISCUSSION; CONSULT WITH SUPERVISOR IMMEDIATELY.

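### The stop note after B7 ends the suicidality interview once a plan is reported, yet Appendix W requires every Module B question to be asked

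*Protocol*

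**What the plan says.** Appendix W applies when a woman being screened endorses items that suggest suicidal ideation. Step 1 refers the screener to Appendix E, Module B, and is emphatic: "The screener MUST ask all of these questions to adequately assess" suicide risk. It adds that the questions cover, among other things, "the specifics of a potential suicide plan, and the individual’s history around suicidality". Step 2 deals with the woman who has a plan: "the screener will ensure that they have all the information about this plan using the SLAP acronym". Only after that does the screener choose a course of action by level of risk.

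Appendix E, Module B, contains the questions themselves. After B5 it prints "IF NO TO B5, SKIP TO B7", and after B7 (a suicide method or plan in mind) it prints "IF NO TO B7, SKIP TO B9". Between B7 and B8 stands this note: "IF PARTICIPANT HAS A SUICIDE PLAN OR RESPONDS ‘YES’ TO ANY OF THE ITEMS FROM B7 ONWARD, END INTERVIEW AND REFER TO ALTERNATIVE RESOURCES". The next item, B8, is "Intend to follow through on a suicide plan". B9 to B12 cover intent to die, preparation, self-injury and attempts in the past month, and B13 asks about a lifetime attempt. The diagnostic box that closes the module sums the points over B1 to B13 to classify current risk.

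**The concern.** A yes at B7 triggers both instructions for the same woman, and a screener cannot follow both as printed. Ending the interview at the note means B8 to B13 are not asked. Asking all of Module B means the note is ignored.

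The stakes are safety at screening. A screener who follows the form stops asking about intent, preparation and attempts just after a woman has reported a plan. Appendix W wants those answers before the screener decides how urgently to act. Its responses range from a referral to the local mental health clinic, through physician or emergency room, to a 911 call.

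**Working it through.** The document gives no figure to reproduce here. The check traces the printed routing and counts what is lost.

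**Inputs (Appendix E, Module B).** Numbered items B1 to B13, so 13 items. Points for a yes: B2 1, B3 1, B4 4, B5 6, B6 8, B7 8, B8 8, B9 8, B10 9, B11 4, B12 9, B13 4. Risk box: Low 1–8, Moderate 9–16, High printed as above 17.

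**Can B8 be reached?**

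| Step | Answer | Goes to |
|---|---|---|
| B5 | no | B7 |
| B5 | yes | B6, then B7 |
| B7 | no | B9 (B8 skipped) |
| B7 | yes | interview ends (B8 not asked) |

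Every route passes through B7, and neither answer to B7 leads to B8. Running all 2^12 = 4,096 yes/no patterns for B2 to B13 through these rules confirms it. B8 is asked in 0 patterns with the note in force and in 2,048 without it (every pattern with B7 = yes).

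**How much is lost?**

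- Stop at B7: B8 to B13 unasked = 6 items; 6/13 = 46%.
- The note also covers a yes to later items. A stop at B9 leaves B10 to B13 (4 items), at B10 leaves 3, at B11 leaves 2 and at B12 leaves 1.
- B1 to B12 refer to the past month. B13 is the only lifetime item and lies beyond the stop, although Appendix W expects the questions to yield the woman's history.

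**Effect on the module's own score.** The unasked items carry 8 + 8 + 9 + 4 + 9 + 4 = 42 points. The most that can be scored up to and including B7 is 1 + 1 + 4 + 6 + 8 + 8 = 28, against 28 + 42 = 70 for the full module. Two examples:

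- Yes to B5 and B7 only, then stopped: 6 + 8 = 14, Moderate. If she would also have said yes to B8: 14 + 8 = 22, High.
- Yes to B7 only, then stopped: 8, Low. If she would also have said yes to B9 and B10: 8 + 8 + 9 = 25, High.

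The total over B1 to B13 that the diagnostic box asks for therefore cannot be completed for any woman who says yes at B7.

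**Are the two instructions reconcilable?** The same end-and-refer wording appears in the psychosis module (Module G), where it serves as an exclusion rule, and Appendix B has a similar rule to refer anyone screened out. So the note can be read as *she is not eligible* and not as *stop assessing her risk*. On that reading the step 2 plan questions and the Appendix W actions still apply. But the note does not mention Appendix W, and Appendix W makes no exception to asking every question. The conflict over B8 to B13 remains.

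**The case against.** The strongest reply is that the note is only a screen-out rule and that Appendix W, as the dedicated suicide-risk procedure, governs. There is support for this:

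- The note refers to any item from B7 onward. That range includes B8, an item which the literal reading makes unreachable.
- The box at the end of the module sums B1 to B13, which presupposes a completed module. It also tells the screener to consult a supervisor immediately if risk is above Low.
- Appendix W will often be in force before B7, because ideation can already be reported at B3 to B5.
- Appendix W's examples of high risk (a specific plan, a lethal and available method, limited resources) are the details gathered in step 2, and the 911 call depends on whether the plan appears immediate. Neither is tied to the Module B score.
- Module B has ordinary skips, so *all* cannot be wholly literal.

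Much of this stands. The screen-out reading is the probable intent, the step 2 questions and supervision limit the harm, and nothing shows that a woman with a plan would receive a lesser response. But the reply depends on the screener inferring the intent from a form that says to stop, with the note placed before the items in question. The ordinary skips do not explain the loss either, since B9 to B13 have no such skip after a yes at B7 and only the note removes them. Step 2 asks about specificity, lethality, availability and nearness of help. It does not replace the intent, preparation and attempt answers that step 1 requires.

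**Conclusion.** The point holds. Read as printed, the note after B7 contradicts Appendix W step 1. It leaves 6 of 13 items (46%) unasked for a woman who reports a plan, including the only lifetime item, and B8 cannot be asked of anyone. This rests on the printed skip rules and on reading the note at its printed position. The counts are of items and answer patterns, not of women, and the document does not show how many women would be affected.

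The consequence is limited to risk assessment at screening. A woman with a plan is excluded before randomisation under either instruction, so sample size, endpoints and the treatment comparison do not change. It should be corrected because it concerns safety and the correction is simple.

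**What to change.** Keep the trigger in the note after B7 and replace its action with: *Screen out and stop the eligibility interview; complete Module B (B8–B13) and the SLAP questions, then follow Appendix W.*

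This makes B8 reachable, restores B9 to B13, allows the module's total to be computed and aligns the two appendices. The cost is one line in a screening appendix and a few more minutes on the call with a woman who reports a plan. Sample size and analysis are unaffected.
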